Participating CSSS are responsible for implementation of the PCMR, and for setting up local coordination committees to oversee project planning and implementation, and to follow up on the project evaluation. In each CSSS, the local committee will set up a clinical committee responsible for the clinical tools and contents needed to implement the project. The ASSSM will provide regional leadership and organizational support required to implement the program in CSSS. Mechanisms will be put in place to encourage primary care physicians to participate (e.g. early involvement of primary care physicians in developing the program and within local coordination committees; support for the project from professional associations; meetings in primary care clinics to enlist the cooperation of physicians). Furthermore, financial compensation is available from the RAMQ (Québec's health insurance board) for general practitioners who help organize clinical projects in a CSSS territory.

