### Research Questions and Objectives

#### Objective 1

To evaluate the effects of the PCMR and their persistence on patients registered in the program and the practices of their primary care physicians, by implementation site and degree of exposure to the program.

For patients, the program should result in improved lifestyle habits and better control of their diabetes and/or their hypertension. Chronic illness management and follow-up should be noticeably improved, as should patient self-management and quality of life. Closer and better coordinated follow-up should also improve certain elements of the patients' experience of care with their primary care physicians (continuity of information, comprehensiveness and perceived outcomes of care). Finally, controlling their condition is likely to lead patients to use health services more appropriately (fewer visits to emergency and fewer hospitalizations for problems related to diabetes or hypertension). In all likelihood, these effects on patients will vary depending on the setting (CSSS) and degree of exposure to the PCMR. As regards medical practice, PCMR implementation should be reflected in participation in the program (continuous medical education activities, use of clinical tools, referral of patients to cardiometabolic risk education centres), interprofessional collaboration and patient management interventions. Persistence of effects on both patients and medical practice remains to be demonstrated.

#### Objective 2

To assess the degree to which the PCMR has been implemented in each participating CSSS territory (local services network) and identify the context-related factors (coercive, normative and mimetic pressures) that could explain the level of implementation.

The aim is to answer the following research questions: To what degree has each setting implemented the program? What contextual factors facilitate or hinder program implementation? To what extent is program sustainability assured: does the PCMR fit into CSSS program activities?

#### Objective 3

To establish the relationships between the observed effects (Objective 1), degree of implementation of the program and contextual factors (Objective 2).

This objective implies the following research questions: How do variations in PCMR implementation influence the effects observed? To what extent do the contextual factors that facilitate or hinder program implementation influence the observed effects?

#### Objective 4

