## Methods/Design

### Design

PCMR evaluation includes analysis of its implementation and of its effects. We posit that the program concept and implementation will adjust to the different CSSS settings. The proposed evaluation will use a mixed design that involves two complementary research strategies [35]. The first strategy is a quasi-experimental "before-after" design, based on a quantitative approach; it will look at the program's effects and their variations among the six settings where it is implemented. This situation corresponds to a natural experiment in which researchers have no control on the intervention being introduced.

The second strategy is consistent with a multiple case study approach, where each of the six settings constitutes a case. This strategy is based on qualitative methods and will characterize the variable represented by the implementation context. A monograph for each setting will be produced following analysis and will include data on the various indicators described below. The monographs will explain the processes that have led to the effects observed and the particular contextual conditions that can be linked to differences in implementation and effects. Adding this component to the evaluation will therefore increase both internal and external validity.

The two strategies will generate data that we will triangulate to provide a deeper explanation of the link between degree of program implementation, context and observed effects. Triangulation will be based on an interpretative analysis of the data collected and on a validation process with individuals responsible for implementing the PCMR through discussion groups that will also serve as mediums for knowledge translation and exchange.

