Indicators for health services utilization by patients in the PCMR, their experience of care, follow-up of diabetes and/or hypertension, self-management and quality of life will be measured using a 20-minute self-administered questionnaire, in French or English, given to patients by the nurse or nutritionist at the cardiometabolic education centre upon program entry, and at 12 and 24 months of follow-up (Additional file 2 and Additional file 3). The questionnaire will be completed on site, with support provided for patients with low literacy levels when required. A postal questionnaire will also be administered 36 months after onset of follow-up (Additional file 3). Data collected at 36 months--a year after the end of follow-up in the program--will be used to check the persistence of effects post-intervention. The first section of the questionnaire focuses on patients' utilization of health services (medical visits, hospitalizations, visits to emergency) during the previous year. The second section documents patient affiliation to the primary care physician who provides diabetes and/or hypertension follow-up and who referred him or her to the education centre, the characteristics of affiliation (duration, frequency and place of consultation), as well as certain attributes related to the patient's care experience with this physician (accessibility, continuity, comprehensiveness and perceived care outcomes). Questions in this section are adapted from the population survey questionnaire developed for a study carried out by our research team aimed at assessing the evolution of primary healthcare organizations and their performance (2005-2010) in two regions of Québec province [36]. Section 3 of the questionnaire concerns management and follow-up of chronic illnesses. These questions are adapted from the *Patient Assessment of Chronic Illness Care *questionnaire [11]. The 4^th ^section is on patient self-management and quality of life related to their diabetes and/or hypertension. Self-management is measured using questions adapted from the *Summary of Diabetes Self-Care Activities*, and assesses the frequency of self-management behaviours during a typical week (preventive behaviours--diet, physical activity, smoking abstinence--as well as compliance with medication as prescribed, glycemia and BP monitoring) [37]. Questions measuring patients' quality of life are adapted from the questionnaire *Audit of Diabetes Dependent Quality of Life *[38-40]. Data on patients' sociodemographic characteristics and health status are the subject of the last section of the questionnaire. Linking patient data to data collected from his or her physician will allow us to determine how primary care services are organized at the place where the patient is seen. A questionnaire will also be administered to patients who withdraw from the PCMR prematurely; it will include questions designed to document the reasons why a person drops out (Additional file 4).

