**Indicators concerning the impact on medical practice **will be measured for participating general practitioners using a 15-minute self-administered mail-in questionnaire, in French or in English, the first time one of his or her patients attends the cardiometabolic risk education centre, and then at 12, 24 and 36 months (Additional file 5 and Additional file 6). In addition to questions pertaining to physicians' sociodemographic and professional characteristics, the questionnaire also documents the organizational characteristics of their clinics using questions from the 2010 survey of primary care clinics used in our previous project [36]. One section of the questionnaire deals with physicians' practices regarding management of patients with diabetes or hypertension; these questions are adapted from the questionnaire by Nutting et al. [44]. The questionnaire for physicians administered at 12, 24 and 36 months includes several questions on their assessment of the PCMR: participation in the program, impacts on their patients and on their practice, relationships with specialized services, strengths and weaknesses of the program, as well as barriers and facilitating factors. The data analysis strategy will be similar to the one used to assess the effects of the program on patients. Physician and clinic characteristics will be utilized as covariables to construct regression models that measure the program's effects on their management of chronic diseases and their perceptions of the effects on patients and on their own practice.

#### Objective 2

Two elements are required to meet the goals. The first consists in assessing the level of PCMR implementation in various CSSS based on four criteria: 1) completeness of the components with regard to the program initially planned by the ASSSM; to assess the degree of implementation, we will measure the differences between the program planned by the ASSSM and the one actually implemented in CSSS; 2) intensity of the effort made to conduct program activities (e.g. number of training sessions, number of patients); 3) integration of the PCMR into CSSS program activities; and 4) program penetration rate among the targeted populations. This will be estimated by calculating the proportion of patients with diabetes or hypertension followed in the PCMR among patients with diabetes or hypertension in each participating CSSS territory (estimated using the medical services and hospitalizations administrative data).

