### Strengths and limitations of the proposed project

Our project has both strengths and weaknesses. Strictly speaking, for a comparative analysis, the number of CSSS in our study is relatively small. However, for a multiple case analysis strategy, this number is sufficient to show contrasts and can rather be seen as a strength of our study. The absence of a control group is a limitation but in this type of study, it is impossible to use an experimental design; we replaced it with a quasi-experimental design [47] and a hybrid analysis strategy that combines quantitative and qualitative aspects. Triangulation increases internal but also external validity, which is often lacking in experimental designs. Moreover, although the 40-month observation period is long enough to show the effects of the PCMR and to document the implementation process, it may not be sufficient to estimate, over the longer term, the sustainability of the effects and of activities undertaken.

Some of the strong points of our study include the fact that it will enable us to fill certain gaps in knowledge and, more particularly, to evaluate the application of the CCM to a primary care "case management" approach rather than to "disease management". It will also allow us to evaluate CCM implementation from a systemic perspective based on the will of the ASSSM to completely implement the proposed program in all Montréal CSSS. Mostly, our study will identify the contextual factors that can modulate the effects of the CCM and that can be associated with successful implementation and with the effectiveness of such a program. These contextual elements will enable us to extrapolate our results to other contexts with similar conditions as well as to other chronic illnesses. The study will also allow us to assess the impact of implementing a program inspired from the CCM on consolidation of local services networks. Finally, in terms of the methodology, we should add that other strengths of the project are sample size, repeated number of observations and use of numerous tools (questionnaires) that have either been validated or used in our previous studies.

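### The first physician questionnaire follows referral and may follow training and tools, so change in diabetes and hypertension management may be measured from a partly exposed baseline

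*Protocol article*

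**What the plan says.** In the Methods, under Objective 1 (the paragraph on medical practice, after Patient recruitment and power calculation), participating general practitioners receive a mailed questionnaire "the first time one of his or her patients attends the cardiometabolic risk education centre, and then at 12, 24 and 36 months". No earlier measurement of the individual physician is described. The 2010 clinic survey is cited there as a source of questions on clinic organisation, not as a pre-programme measure of how these physicians manage patients.

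The same paragraph has a section on management of patients with diabetes or hypertension. Questions on participation in the programme and its perceived impact are described for the 12-, 24- and 36-month questionnaires. The analysis is to resemble the one for patients, which uses before-after differences and longitudinal models.

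The description of the patient questionnaire identifies the treating physician as the one "who referred him or her to the education centre". The section on initiatives in Montréal makes continuing medical education and clinical tools the support directed at physicians. It also plans ways to bring physicians in, among them "meetings in primary care clinics to enlist the cooperation of physicians".

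The Design section calls the quantitative strategy quasi-experimental and before-after. The limitations section says: "The absence of a control group is a limitation but in this type of study, it is impossible to use an experimental design". It does not mention the timing of the physician baseline.

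**The concern.** For patients, entry to the education centre is a natural time zero, because their clinical process starts there. The physician questionnaire borrows the same anchor, but the physician's own exposure can start earlier, with training, tools and the act of referring.

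With no control group, the first wave has to stand in for practice without the programme. If practice has already moved by then, part of the effect sits in the baseline. That matters for the medical-practice half of Objective 1 and for the part of Objective 3 that relates implementation in each CSSS to medical practice. Patient outcomes are not affected.

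**Working it through.** The document gives no figure for this point, and the patient power calculation does not bear on it. The check is the order of events, followed by a simple identity.

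**Order of events for one physician**

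1. The CSSS bring physicians in through early involvement in developing the programme, local committees and clinic meetings (section on initiatives in Montréal). This step is encouragement to take part, not yet treatment.
2. Medical education and clinical tools are provided (same section). The document does not say whether this comes before or after the physician's first referral.
3. The physician refers a patient (patient questionnaire description, Objective 1).
4. The patient attends the centre, and this triggers the first physician questionnaire.
5. Further questionnaires follow at 12, 24 and 36 months.

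Step 3 certainly precedes the first wave. Step 2 may precede it, wholly or in part.

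**Which outcome is affected.** As described, the first wave holds physician characteristics, clinic organisation and the diabetes/hypertension management section. The first two are to serve as covariates. The management section is therefore the practice outcome described at the first wave that can be compared over time.

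**Size.** Let D be the full change in practice from before any exposure to follow-up, and f the share of D already present at the first questionnaire.

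Observed change = D − fD = (1 − f)D

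| f (assumed) | share of D observed |
|---|---|
| 0.10 | 1 − 0.10 = 90% |
| 0.25 | 1 − 0.25 = 75% |
| 0.50 | 1 − 0.50 = 50% |
| 0.75 | 1 − 0.75 = 25% |

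**Differences between CSSS.** Take two sites with the same D, one with f = 0.2 and the other with f = 0.6. They show 0.8D and 0.4D, a ratio of 0.8/0.4 = 2 with no true difference. These values are also assumed, and the ratio only restates them.

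**Why f may vary.** Two facts in the document make a uniform f doubtful:

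- Recruitment runs 28 months, so a physician whose first patient attends late may have had a long prior period of programme activity.
- One of the six sites has had a diabetes referral centre since 2006.

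**Objective 3.** Number of training sessions is an example of the intensity criterion for implementation (Objective 2). If those sessions include physician education given before first referral, the same variable that should predict a larger effect also raises f. The estimated association could then be flattened.

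**The case against.** **How much exposure there is.** Only one referral is certain before the first questionnaire. Being enlisted is not the same as being trained, and shared follow-up and information from the centre start only around that first attendance, so the first wave may still be early. This stands. It limits the point to a possible and partial exposure of unknown size.

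**What the plan already covers.** Start-up interviews record activities already in place in each territory, and effects are to be modelled by CSSS and degree of exposure. This helps at site level but does not date exposure for each physician. The first physician questionnaire (Additional file 5) is not shown, so retrospective items on earlier practice or training cannot be excluded.

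**Feasibility.** The researchers do not control the intervention, and the CSSS run enlistment. Surveying every physician before contact needs a roster that the team is not said to have. This also stands, so an earlier mailing can only be a conditional recommendation.

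**Two stronger readings do not hold.** Objective 1 lists, under participation, "continuous medical education activities, use of clinical tools, referral of patients to cardiometabolic risk education centres", and a reader might infer that referral is a before-after outcome fixed at 100% from the start. The plan does not describe that contrast. Participation items are listed only for the later waves, where uptake can be described and compared without a prior value. A reader might also infer that surveying only referring physicians is a selection error. Objective 1 is about the practices of the physicians of registered patients, so this is its stated scope.

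**Conclusion.** The point holds in a limited form. The first physician questionnaire is certainly after a referral and possibly after training and tools. In an uncontrolled before-after design, change in diabetes and hypertension management may therefore be measured from a partly exposed baseline, and the limitations section does not say so.

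The direction is towards understatement if early exposure improves practice. The size is unknown: the document gives no value of f, so the percentages above are illustration and not estimates. That f differs between CSSS is plausible from the 28-month recruitment and the site active since 2006, but it is not shown. If it does differ, both the between-CSSS comparison of physician change and the implementation-effect link for medical practice in Objective 3 can be distorted. More follow-up waves would not repair this.

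**What to change.** 1. Add three items to the existing first physician questionnaire: date of first programme training, date clinical tools were received, and date of first referral.
2. Model change in the management section by exposure status, or duration of exposure, at the first questionnaire.
3. Add a sensitivity analysis restricted to physicians with no prior training or tools at that point.
4. Report the result as change since first patient attendance, not as the full programme effect, and name the timing among the limitations.
5. Where a CSSS can supply contact lists, send the same questionnaire at first clinic contact. Physicians involved earlier in developing the programme would still have had some contact by then, so the dates are needed for them too.

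The cost is a few extra items, some recall error in the dates, and possibly a lower response to an earlier mailing from physicians not yet committed. The restricted analysis will have fewer physicians, and the document does not allow their number to be predicted.

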The second element includes an analysis of factors influencing program implementation [45]. The goal of the analysis is to understand how and why the PCMR has evolved and adapted to its context over time. It will put into perspective what program elements that are truly implemented contribute to the effects produced and will evaluate the generalizability potential of the program to other contexts. In terms of contextual determinants of program implementation, we looked to the conceptual framework on factors to consider to produce change in organizations, developed by Champagne [46]. We consider that implementation results from the climate in which the program is implemented (itself influenced by management strategies and incentives used), the level of trust and involvement of stakeholders, the organizational structure that is likely to help or hinder implementation, and collective leadership and training. This component will also examine contextual factors that explain PCMR implementation in terms of the influences of various actors from the local services network. The ASSSM and the CSSS can have a coercive influence because of their position of authority and the significant resources they contribute. Through their professional associations, professionals collectively and individually have normative influences. In each local services network, there are also dominant organizations whose practices are considered to be exemplary by other partners, who tend to emulate them. These dominant organizations have a mimetic influence (e.g. FMG, network clinics).

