Data will be collected in three phases, as per the program implementation stages. Semi-structured interviews with individuals from the ASSS and CSSS responsible for program implementation are scheduled for the beginning of the project (start-up phase). They will provide an initial portrait of regional services organization related to the activities of the program being implemented and will document the program components (objectives and purposes, roles and actors involved, resources and activities). They will also be used to define the dynamics in each implementation site. Interviews with respondents from each territory will focus on local historical contexts of interventions with people at risk of or who have diabetes or hypertension; organizational contexts of the CSSS; PCMR activities already in place and their components; local resources allocated; number of medical clinics and physicians involved; and number of patients targeted by the program. A second and third round of semi-structured interviews with local and regional respondents will be conducted 20 and 40 months after the beginning of the program. They will document PCMR activities actually implemented and degree of program implementation, activities set up to integrate the PCMR into the CSSS's regular activities, and obstacles and facilitators encountered. The questionnaires for physicians will also document barriers and facilitators. These contextual determinants will be grouped by dimension and conveyed with descriptive variables. The interview grids used at the beginning of the implementation of the project are included in Additional files 7a and 7b. Data collection tools that will be used 20 and 40 months after the beginning of the program will be constructed after analysis of the data collected at the beginning of the implementation of the project.

Based on the information collected throughout the project, a descriptive analysis of each case (implementation setting) will be performed. Six monographs, one for each setting, will describe the phases of PCMR implementation and its explanatory factors.

#### Objective 3

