Two approaches will be used to attain this objective. The first is designed to complement the analysis proposed in Objective 2. Using the material compiled in the monographs, quantitative variables and categorical taxonomic variables will be created and integrated into regression analyses explaining the effects of the program. Regression models will be built to assess the influence of the variables pertaining to PCMR set up and implementation in the various CSSS on the effects observed among patients, controlling for degree of exposure to PCMR, patient characteristics and the characteristics of primary care clinics where they are seen. Given the low number of upper level units (6 CSSS), variables linked to CSSS will be considered as fixed effects in regression models. Linear regressions will be constructed for continuous dependent variables, while logistic models will be used for dichotomous dependent variables and multilevel longitudinal models for dependent variables that are the object of repeated measures. A similar analysis strategy will be used to assess the influence on medical practice of variables that reflect PCMR set up and implementation in various CSSS.

The second approach will be interpretive: from the material used to produce the monographs, participants' statements on the relationship between program effects and components will be noted and analyzed. Conclusions drawn from these two approaches will be validated in discussion groups.

#### Objective 4

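### Objective 3 lets judgement-based implementation and context variables be coded from monographs that already report and explain the site effects, with no stated safeguard

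*Protocol article*

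**What the plan says.** Three parts of Methods/Design in the protocol article bear on this.

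- **Design** sets the content and timing of the site monographs: "A monograph for each setting will be produced following analysis and will include data on the various indicators described below". The indicators described later include the patient effects (HbA1c, blood pressure and others). It adds: "The monographs will explain the processes that have led to the effects observed and the particular contextual conditions that can be linked to differences", meaning differences in both implementation and effects.
- **Objective 2** gives a narrower account: "Six monographs, one for each setting, will describe the phases of PCMR implementation and its explanatory factors". It plans on "assessing the level of PCMR implementation in various CSSS based on four criteria": completeness, intensity, integration and penetration. The same section says of its analysis of contextual factors: "It will put into perspective what program elements that are truly implemented contribute to the effects produced". It also draws context information from physicians: "The questionnaires for physicians will also document barriers and facilitators".
- **Objective 3** derives the explanatory variables: "Using the material compiled in the monographs, quantitative variables and categorical taxonomic variables will be created and integrated into regression analyses". The dependent variables are the effects on patients and, by a similar strategy, on medical practice.

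The article does not say who assigns the codes, when they are fixed, or what the coders will have seen.

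**The concern.** Objective 3 asks whether the degree of implementation and the local context go with better effects. The article presents this as a central contribution and as the basis for extrapolating to other settings. Such an association is informative only if a site's code could have disagreed with its results. If the code is drawn from a document that already reports those results and offers an explanation for them, the coder can move towards agreement without intending to. The regression would then partly return the interpretation that was put into it.

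The planned cross-checks would not expose this well. The interpretive approach draws on the material behind the monographs, and validation takes place in discussion groups with people responsible for implementing the programme. Neither is independent of the coding material.

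**Working it through.** **Step 1: the order of work.** The plan states no figure on this point, so the first check is textual.

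1. Design: the monograph holds the indicator data and explains the effects.
2. Objective 3: codes are created from monograph material.
3. Objective 3: the effects are regressed on those codes.

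Followed literally, this places knowledge of the effects before the coding. The Design sentence on timing could mean that the monographs follow the case analysis and not the effects analysis. But a document of which it is said that "The monographs will explain the processes that have led to the effects observed" cannot be completed before the effects are known. Under the Objective 2 description, where the monographs cover implementation and its determinants, the codes could be assigned without sight of the effects. The two descriptions are therefore compatible with different procedures.

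**Step 2: which variables are exposed.**

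- *Intensity and penetration:* largely counts (training sessions, patients, a proportion with a denominator from administrative data). Low exposure.
- *Completeness and integration:* a comparison of the planned with the delivered programme, and absorption into regular activities. These need judgement, and the article states no scoring rule.
- *Taxonomic and context classes:* the dimensions are named in advance, but the classes are built from monograph material. Highest exposure.
- *Medical-practice arm:* physicians report barriers and facilitators on the same questionnaire as their practice and perceived impacts, so part of the context material and the outcome share a respondent and an instrument.

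**Step 3: how much coding freedom can matter with six sites.** This is an illustration.

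From the article: 250 × 6 × 28/12 = 3500 patients; 3500 × 0.80 = 2800 after attrition; 6 sites; significance level 0.05.

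Assumed: equal sites, so n = 2800/6 ≈ 467; outcome in SD units; no true site differences; a binary site code tested as a fixed effect.

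- Standard error of a 3-versus-3 contrast: √[(1/n)(1/3 + 1/3)] = √(0.6667/466.7) = 0.0378 SD. A difference above 1.96 × 0.0378 = 0.074 SD is declared significant.
- Distinct 3/3 codes: C(6,3)/2 = 10. All distinct binary codes: (2⁶ − 2)/2 = 31.

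| How the code is chosen | Type I error (100,000 simulations) |
|---|---|
| One 3/3 split fixed without sight of outcomes | 4.9% |
| Best-fitting of the ten 3/3 splits | 31.8% |
| Best-fitting of all 31 binary codes | 43.0% |

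Plausibility check: ten independent tests would give 1 − 0.95¹⁰ = 40.1%. The ten splits share sites and are correlated, so a figure below 40.1% is expected.

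**The case against.** A reader might infer that the coders will be unblinded and that Objective 3 is circular. The documents do not support either as fact.

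- **Blinding.** The article is silent on who codes and when. A condensed article may leave that to the full protocol, and the Objective 2 description leaves room for coding from implementation material alone.
- **Circularity.** Biological and lifestyle outcomes come from the regional registry, and utilisation is also documented from administrative data. Neither is derived from the monographs. Four implementation criteria and the main context dimensions are stated in advance, and some criteria are countable.
- **Timing.** A halfway meeting is to discuss the degree of implementation, and the second interviews are at 20 months, before any patient has a 24-month measure. Some implementation results will therefore predate the final effects.
- **Purpose.** This is a formative evaluation with a case-study arm, in which explaining effects in context is a declared aim.

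All of this stands, and it narrows the point to the judgement-based variables. It does not remove the point, because the difficulty comes from a stated workflow and not only from an omission. The halfway assessment guarantees nothing: 12-month data may exist by then, and a 40-month interview round follows. Explaining effects in context is compatible with fixing the codes first.

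**Conclusion.** The point holds in a limited form. As written, Design and Objective 3 together permit the completeness and integration scores, and above all the taxonomic and context classes, to be coded from monographs that already report and explain site effects. No safeguard is stated, and the Design and Objective 2 accounts of the monographs must be reconciled.

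The size of any bias cannot be known from the article. About 32%, against about 5% for a code fixed blind, is an upper illustration for 3/3 splits. It assumes equal sites, no true differences and a code picked purely to fit the outcome, and the plan specifies no binary or 3/3 coding. Realistic coding would probably fall between the two. The chance that a blind 3/3 split would coincide with the three best sites (1 in C(6,3) = 20) describes accidental agreement and does not measure bias.

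The matter should be settled before coding starts, because it cannot be repaired once coders have seen the effects.

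**What to change.** State one order of work and use it in Design, Objective 2 and Objective 3.

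1. Score the four implementation criteria and assign the context classes for each CSSS from the start-up, 20-month and 40-month interviews and from programme or administrative records. Exclude physician-perceived impacts from this material.
2. Date and lock the scores before any site-specific effect is released to the coders. Since results are shared during the project, the restriction should also cover interim feedback to them.
3. Then add the effects and the explanatory section to the monographs.
4. Label any variable created after the lock as exploratory.

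The cost is a few sentences and a reordering of existing work, with no new data. The downside is small: factors discovered late can be reported only as exploratory. One limit remains: respondents interviewed at 40 months may hold their own view of how their site performed, and a lock on the scores does not remove that.
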